## Abstract

**Background:**

There is scientific evidence suggesting that app-based interventions targeted to increase the level of physical activity might be effective, although multicomponent interventions appear to be more effective than app-based interventions alone. Despite the motivating results, it remains unclear whether or not app-based interventions can increase the level of physical activity and cardiovascular health. Our study aims to investigate the effect of a smartphone app combined with gamification on the level of physical activity of adults and older adults. The specific aims are (1) to verify the effects of the intervention on cardiometabolic and cardiovascular health, lung function, and cardiorespiratory fitness; and (2) to verify the relationship between age group and the response rate.

**Methods/design:**

We will conduct a sequential multiple assignment randomized trial (SMART). The adaptive intervention protocol will last 6 months. After baseline assessments, participants will be randomized into one of three groups (group 1: app + tailored messages; group 2: app + tailored messages + gamification I; control group: physical activity counseling). For 12 weeks, we will record the average number of steps per day of participants from groups 1 and 2. At 6 weeks from initiation of recording, participants will be classified into responders and non-responders according to their increase in the average number of daily steps; all those considered as non-responders will be re-randomized, with the chance to participate in a third group – group 3: app + tailored messages + gamification II. Finally, at 12 weeks, participants will continue using the app but will no longer receive direct intervention from investigators. All participants will be reassessed at 3 and 6 months from baseline. Our pilot SMART will require 42 participants (14 per arm). Following the SMART pilot, we will calculate the sample size for the trial based on the variation of the average number of steps/day, including an up to 40% loss to follow-up and a less optimistic nonresponse rate of 65%.

**Discussion:**

To our knowledge, this will be the first trial with adaptive intervention to test the effectiveness of using a smartphone app to increase the level of physical activity of adults and older adults.

**Trial registration:**

Brazilian Clinical Trials Registry: RBR-8xtc9c. Registered on 3 August 2018, http://www.ensaiosclinicos.gov.br; UTN number: U1111–1218-1092.

## Background

Popular technologies such as smartphones and their applications (apps) have been used as tools to engage people who do not meet the recommended levels of physical activity. There is scientific evidence with moderate effect (weighted effect size = 0.54) suggesting that app-based interventions targeted to increase the level of physical activity might be effective [1], although multi-component interventions appear to be more effective than app-based interventions alone [2]. Apps intended to improve cardiovascular health should include features such as privacy policy and reliable sources of information and should be mainly designed using behavior change theory [3]. It is believed that the development of apps based on behavioral change techniques may contribute to the emergence of cognitive patterns favorable to the practice of physical activity.

The main effective components of apps are most likely personalization and gamification [4]. Interestingly, the adherence rate to an app-based intervention was not significantly different in comparison to conventional intervention [5]. However, despite its increasing use, smartphone apps for physical activity lack a scientific basis. Among many health and fitness apps, only a few are based on behavior change techniques [2, 6–8].

The use of games for promoting healthy lifestyle behaviors (such as physical activity) has been shown to be effective [9], introducing gaming elements as novel opportunities for behavior change techniques, increasing enjoyment and, thus, intrinsic motivation. The use of game elements outside of the game context is called gamification and has been increasingly used for promoting healthy lifestyle behaviors. Among gaming elements, goal-setting with feedback and rewards are the most frequently used. Social connection, progress bars, and challenges/quests have also been investigated in a smaller number of studies [10]. Studies have also shown that there is a limited theoretical foundation for gamification, and most studies have used goal-setting as a motivation strategy to engage people in playing the game [10].

Among the main limitations of the available apps, with or without game elements, is the long-term adherence to app-based interventions [10, 11]. Despite the motivating results, it remains unclear whether or not app-based interventions can increase the level of physical activity and cardiovascular health.

## Methods

This study protocol was written according to the Standard Protocol Items: Recommendations for Interventional Trials (SPIRIT) 2013, and the SPIRIT checklist is available in Additional file 1.

### Aims and design

The primary aim of our study is to investigate the effect of a smartphone app combined with game elements on the level of physical activity of adults and older adults, measured by the average number of daily steps. The secondary aims are (1) to verify the effects of the intervention on cardiometabolic and cardiovascular health, lung function, and cardiorespiratory fitness; and (2) to verify the relationship between age group and the response rate.

We will conduct a Sequential Multiple Assignment Randomized Trial (SMART). This study was approved by the Ethics Committee of the Federal University of Sao Paulo (# 0499/2018) and is registered in the Brazilian Clinical Trials Registry (RBR-8xtc9c).

The SMART design has been recommended over the classical randomized controlled trial for technology-based interventions [12, 13] as it allows adaptations over time based on the participants’ response to the intervention. Despite the large potential and shown feasibility [14], the SMART design has, thus far, hardly been conducted in smartphone and gamified interventions.

The adaptive intervention protocol will last 6 months. Initially, participants will be randomized into one of three groups (group 1: app + tailored messages; group 2: app + tailored messages + gamification I; control group: physical activity counseling) (Fig. 1). Over 12 weeks, we will record the average number of steps per day for each participant from groups 1 and 2. At 6 weeks from initiation, participants will be classified into responders and non-responders according to the targeted average number of daily steps; all those considered as non-responders will be re-randomized, with the chance to participate in a third group – group 3: app + tailored messages + gamification II (Fig. 1). At the end of the 12 weeks, participants will continue using the app but will no longer receive any direct intervention from investigators. All participants, including those in the control group, will be reassessed at 3 and 6 months from baseline. The protocol timeline is shown in Fig. 2.

**Fig. 1 Fig1:**
[figure not shown]
Study flowchart

**Fig. 2 Fig2:**
[figure not shown]
SPIRIT figure – protocol timeline

Assessors will be blinded to group allocation. We will randomize participants in blocks of six (two to each group) using opaque sealed envelopes and the sequence of group allocation will be computer generated.

Before randomization, all participants will watch a brief animated video about the benefits of practicing physical activity, the minimum quantity of exercise recommended to reach health benefits, and examples of daily-living situations where they can increase their levels of physical activity. They will receive a link to watch the video on the internet as many times as they want and will receive a printed booklet with the same content of the video.

Participants from groups 1 and 2 will have a commercial freely available app installed on their smartphones. This app has gamification functionalities, and it will track their daily steps. Participants will be instructed about the use and functionalities of the app, and they will be encouraged to use the smartphone close to their waist during all activities.

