#### Control group

The control group will receive physical activity counseling, provided by reinforcing the information of the video they watched prior to randomization.

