### Follow-up

After 3 months of intervention, all participants (including those in the control group) will be reassessed. Participants from groups 1, 2, and 3 will be advised to maintain the monitoring of daily steps by the app but will no longer receive any direct intervention from researchers (text messages, virtual challenges, or group meetings). Finally, after 3 months of self-monitoring of the number of steps, all participants will be reassessed and the protocol completed.

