### Sample size

The main objective of a SMART study relies on the feasibility of carrying out a future large-scale trial, rather than investigating the effects of the proposed set of treatments. To reach this goal, we must ensure that the number of subjects will be sufficient and balanced among all of the subgroups. According to Almirall et al. [16], a fixed probability *k* of about 80–90% should be considered so that at least *m* participants would end in non-responders’ subgroups B, C, E and F (Fig. 1). Considering a range of non-response rates in SMART studies of 35–65%, we calculated an *m* of 3 participants per subgroup as sufficient to ensure familiarity with the protocol, treatment delivery, and identification of potential problems. For a non-response rate of q = 50% at the end of the 6th week, our pilot SMART study will require 42 participants (14 per arm) [16].

After conducting this SMART pilot, we will consider the variation on the average number of steps per day to calculate the sample size of the trial, including an up to 40% loss to follow-up and a less optimistic non-response rate of 65%. To increase the feasibility of a future large-scale trial, we will calculate the sample size considering groups A + B (maintain – switch to group 2), groups A + C (maintain – switch to group 3), groups D + E (maintain – switch to group 1), groups D + F (maintain – switch to group 3), and the control group.

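### One fixed, published block size of six lets anyone who influences enrolment and knows the earlier allocations foresee up to 20% of first-stage assignments

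*Protocol article*

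**What the plan says.** The first randomization is described in the protocol article under Methods, Aims and design, in the text after Figure 2. After baseline assessment, "participants will be randomized into one of three groups". The method is: "We will randomize participants in blocks of six (two to each group) using opaque sealed envelopes". The list itself is produced by computer. No stratification and no second block size is mentioned. On blinding, the same paragraph says "Assessors will be blinded to group allocation", and Study measurements repeats this. Nothing is said about blinding participants, intervention staff or the person who enrols.

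The arms differ visibly in what is delivered. The text on the app reads "Participants from groups 1 and 2 will have a commercial freely available app installed on their smartphones". Group 2 is also invited to challenges, with badges and rankings. For the third arm, "The control group will receive physical activity counseling". Follow-up shows that researchers themselves supply the messages, challenges and meetings, because these are what participants stop receiving at 3 months.

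The Sample size section asks for 42 pilot participants, 14 per arm. Trial status reports that recruitment was still open at protocol version 4 (23 October 2019), with completion intended for 15 November 2020.

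**The concern.** Permuted blocks of one known size have a regular structure. Once the earlier cards in a block are known, the remaining ones are constrained, and the last is fixed. An opaque envelope hides the next card but not what can be deducted by counting the earlier ones. Blinded outcome assessors protect measurement, not entry to the trial.

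What is at stake is selection at enrolment. Behavior-change status, which includes willingness to become active, is recorded before randomization and is plausibly related to daily steps, the primary outcome. Some eligibility criteria leave room for judgment, such as familiarity with a smartphone or other health problems that make activity unsafe. Someone who foresees the next group could hasten or delay a motivated candidate. With 14 per arm, two steered entries are 2/14 = 14% of an arm.

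**Working it through.** **Inputs.** Block of six, two per group; three groups at 1:1:1 (Aims and design). 42 participants, 14 per arm (Sample size). Assumption: one unstratified list, since no strata are stated. The article gives no predictability figure to reproduce. As a consistency check, 42/6 = 7 complete blocks and 7 × 2 = 14 per arm, which agrees with the stated numbers.

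**Fully informed observer** (knows every earlier allocation and where blocks start). There are 6!/(2!·2!·2!) = 90 equally likely blocks. A place is certain when all remaining places belong to one group.

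| Place | P(certain) | P(at least one group ruled out) | P(best guess right) |
|---|---|---|---|
| 1 | 0 | 0 | 1/3 = 0.333 |
| 2 | 0 | 0 | 2/5 = 0.400 |
| 3 | 0 | 0.2 | 0.500 |
| 4 | 0 | 0.6 | 0.4 × 1/3 + 0.6 × 2/3 = 0.533 |
| 5 | 3 × (2/6)(1/5) = 0.2 | 1 | 0.2 × 1 + 0.8 × 1/2 = 0.600 |
| 6 | 1 | 1 | 1 |
| Sum | 1.2 | 2.8 | 3.367 |
| Sum/6 | **20.0%** | 46.7% | **56.1%** (chance 33.3%) |

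Over seven blocks the expected number of certain assignments is 7 × 1.2 = 8.4 of 42. Of the 90 blocks, 72 have one certain place and 18 have two, so the realised number lies between 7 and 14.

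**Observer who sees only app versus control.** The exact group can be named only when all remaining places are control: 1/3 (place 6) + 1/15 (place 5) = 0.4 per block, which is 6.7%, or 2.8 of 42. App versus control, without the exact arm, can be foreseen more often. To the 0.4 add runs of app places at the end of the block: 2/3 + 6/15 + 4/20 + 1/15 = 1.333. The total is 1.733/6 = 28.9%.

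**Effect of varying the block size.** Simulation of 3,000 lists of 42, with sizes chosen at random and an observer who knows the possible sizes and all earlier allocations:

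| Sizes | Certain | Best guess right |
|---|---|---|
| 6 only (exact) | 20.0% | 56.1% |
| 3, 6 | 8% | 57% |
| 3, 6, 9 | 3.5% | 55% |
| 6, 9 | 5% | 54% |
| 6, 9, 12 | 2% | 52% |

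Varying the size removes most of the certainty but little of the advantage in guessing. The simulated sizes were not forced to add up to the number remaining. Forcing this gives a knowledgeable observer more to work with near the end of the list.

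**The case against.** A computer-generated sequence, permuted blocks and opaque sealed envelopes are a conventional scheme, and nothing in the text contradicts itself. Four stronger readings are tempting, and the article does not support them.

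- **That 20% of assignments are predictable as a matter of fact.** This needs a person who knows the whole allocation history and the block starts and who also influences enrolment. The article does not say who enrols, opens envelopes or installs the app. A condensed article may leave that to the full protocol, so it cannot be concluded that the roles are not separated. The 20% is a ceiling.
- **That installing the app gives the group away.** Installation does not separate group 1 from group 2. In addition, Intermediate assessment says that all participants use the app for a week after randomization before any intervention. The groups become visible through what is delivered as a whole (messages, challenges, counseling). That staff and participants know the group is a firm inference from this, not a statement in the article.
- **That entry can be steered freely.** Randomization follows baseline visits on two days, 7 days apart, and several criteria are measured (accelerometer steps, spirometry, exercise test). This narrows discretion but does not remove it.
- **That no analysis could repair an imbalance.** Behavior-change status and accelerometer steps are recorded at baseline, so partial adjustment is possible. Unrecorded differences would remain.

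What survives is that the single block size is a stated and published choice. Separating roles in an unseen document would limit who can exploit it but would not make the size unknown.

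**Conclusion.** The point holds as a conditional, minor design weakness. For an observer who knows the earlier allocations and block starts and influences enrolment, 20% of first-stage assignments are expected to be certain in advance (8.4 of 42), and the best guess is right 56% of the time against 33% by chance. For anyone who knows less, the figures are lower. The result assumes one unstratified list and covers the first randomization only; how the week-6 re-randomization is carried out is not described. No actual bias is shown or claimed.

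**What to change.** For envelopes not yet opened, starting at the end of a completed block, regenerate the list with randomly varied, undisclosed block sizes. Sizes 6 and 9 would serve, chosen so that the remaining total still gives 14 per arm. State no sizes in site documents. Avoid blocks of three, because the last place of each is fixed and one in three places is certain if the size is known.

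The total limits what can be done late in recruitment. With 18 places left, the sizes can be 9 + 9 or 6 + 6 + 6, but with 12 left only 6 + 6 fits, and variation gains nothing. How many envelopes remain is not stated.

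Because best-guess success barely changes, the person enrolling should also not see the allocation log. If the full protocol already arranges this, one sentence saying so is enough. If imbalance is suspected, an analysis adjusted for behavior-change status and baseline steps would address part of it. The same scheme should carry over to the larger trial that the pilot is meant to inform.

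The cost is a new list and envelopes, a record of which participants came from which list, and a possible small imbalance if recruitment stops within a block: at most three between two arms in a block of nine, against two in a block of six.

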### Interventions

#### Group 1 – App + tailored messages

Participants will use the app to track the number of daily steps and they will receive weekly text messages on their smartphones, with information about their performance on last week and motivational phrases according to their behavior-change status at the end of the protocol, the responders of Group 1 will end up in the subgroup A, while non-responders will end up in the subgroups B or C.

#### Group 2 – App + tailored messages + gamification I

Additionally to monitoring the number of steps and individual messages, participants will be encouraged to join virtual challenges; for each challenge they complete, a virtual badge will be given. The challenges available will be related to the target number of steps per day, target distance walked in the month, and group competitions where the total number of steps is compared among the different groups of app users. Further, there will be rankings of the number of steps among all users at the end of the protocol, the responders of Group 2 will end up in the subgroup D, while non-responders will end up in the subgroups E or F.

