#### Group 3 – App + tailored messages + gamification II

The second stage of gamification will be available in the protocol by the time of the intermediate assessment (6th week of intervention). Gamification II will include the same features of gamification I, plus opportunities for socialization among participants (biweekly group meetings) and discussion forums about physical activity.

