### Data analysis

Participants’ characteristics will be presented by descriptive statistics. We will use ANOVA tests to compare the effect of interventions on the increase of physical activity levels, cardiovascular and metabolic health, lung function, and cardiorespiratory fitness among groups A + B + C and D + E + F pre- and post-intervention compared to the control group. Additionally, we will use the same test to analyze the effect of interventions on the average number of daily steps comparing the final subgroups (A to F) against the control group as well as the subgroups A + F, B + D and C + E against the control group.

To analyze the relationship between age and the response rate to each intervention, we will group responders and non-responders according to age ranges (20–30 years old, 31–40, 41–50, 51–60, 61–70, and 71 and older) and compare them in subgroups from A to F using Pearson or Spearman correlations (according to data distribution).

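### Gamification II is delivered partly through participant meeting groups, but the ANOVA treats subgroups C and F as independent individuals; if steps correlate positively within groups, standard errors against control are too small.

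*Protocol article*

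**What the plan says.** Randomisation is of individuals, in blocks of six (Aims and design).

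- **Gamification I (group 2):** individual step and distance challenges with badges, a ranking of all users, and "group competitions where the total number of steps is compared among the different groups of app users". The app is a commercial product open to anyone.
- **Gamification II (group 3):** the same features, plus "opportunities for socialization among participants (biweekly group meetings) and discussion forums about physical activity". It is open only from the week-6 assessment. The Sample size section shows that C (from group 1) and F (from group 2) both switch to it, while B switches to group 2 and E to group 1.
- **Control group:** counselling that reinforces the video. No group activity is described.
- **Data analysis:** "We will use ANOVA tests to compare the effect of interventions". The contrasts with control are A+B+C, D+E+F, each final subgroup from A to F, and A+F, B+D and C+E.
- **Sample size:** for the later trial, "we will consider the variation on the average number of steps per day to calculate the sample size of the trial", with allowances for 40% loss and 65% non-response. Clustering is not mentioned.

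**The concern.** Participants who meet every two weeks and share a forum can affect one another's activity, and steps per day is the primary outcome. Controls have no such link. This is a partially nested design: one side of the comparison has a group level and the other does not. An ANOVA on individuals counts each group-3 participant as a separate piece of information. With a positive within-group correlation, the mean for C or F is less precise than the ANOVA reports, its interval against control is too narrow, and the false-positive rate exceeds the nominal level. C and F are also listed as separate subgroups although they enter the same programme, so their results may share a group effect.

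This matters most for planning. The protocol describes the study as a step towards a larger trial, and who met with whom may be impossible to reconstruct if it is not recorded while recruitment continues.

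**Working it through.** **The plan's own figure.** The pilot size is 3 arms × 14 = 42. It rests on a feasibility criterion: three "participants per subgroup as sufficient to ensure familiarity with the protocol, treatment delivery, and identification of potential problems", with a 50% non-response rate. The chance of at least 6 non-responders among 14 at 50% is 0.788 in one app arm and 0.788² = 0.621 in both. No standard error enters this criterion, and group 3 opens only after non-responders are counted, so meeting-group clustering cannot change the 42. Whether 42 meets its own criterion is a separate question.

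**Inputs from the protocol.** 14 per arm and 50% non-response. **Assumptions:** equal re-randomisation, ICC of 0.01, 0.05 or 0.10, two-sided 5% level, all group-3 members in one meeting group, normal approximation.

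Expected numbers: C = F = 14 × 0.5 × 0.5 = 3.5, and group 3 as a whole = 2 × 3.5 = 7.

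**Formulas.** For an arm of n containing one meeting group of size g, the design effect is DE = 1 + g(g − 1) × ICC / n, which is 1 + (g − 1) × ICC when g = n. Against n₀ unclustered controls, the ratio R of true to naive standard error is √[(DE/n + 1/n₀) / (1/n + 1/n₀)], which is √[(DE + 1)/2] when n = n₀. The actual error is 2 × [1 − Φ(1.96/R)].

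**Group 3 as one group of 7, equal n.** The protocol lists no C+F contrast, so this illustrates group 3 as a whole.

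| ICC | DE | R | Actual error |
|---|---|---|---|
| 0.01 | 1.06 | √1.03 = 1.015 | 5.35% |
| 0.05 | 1.30 | √1.15 = 1.072 | 6.8% |
| 0.10 | 1.60 | √1.30 = 1.140 | 8.6% |

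**C alone, or F alone, against 14 controls (n = g = 3.5).** DE = 1 + 2.5 × ICC = 1.025, 1.125, 1.25. R = √[(4 × DE + 1)/5] = 1.010, 1.049, 1.095. Error 5.2%, 6.2%, 7.4%.

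**Pooled D+E+F against control, only F clustered (n = 14, g = 3.5).** DE = 1 + 0.625 × ICC = 1.006, 1.031, 1.063. R = 1.002, 1.008, 1.016. Error 5.0%, 5.2%, 5.4%. A+B+C, where only C attends meetings, gives the same.

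**Negative correlation.** At ICC −0.05 and a group of 7, DE = 0.70 and R = √0.85 = 0.92, so the naive standard error is too large.

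**Later trial, illustration only.** Take the effect size of 0.54 from the Background (not a design input), 80% power and 40% loss. Under independence, 2 × [(1.96 + 0.84)/0.54]² gives 54 per arm, or 54/0.6 = 90 after loss. If a whole arm were in meeting groups of 7, replacing the factor 2 by (1 + DE) gives 56, 62 and 70 at the three ICCs, or 94, 104 and 117 after loss. The planned strategies A+C and D+F include responders who attend no meetings, so their increase would be smaller.

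**The case against.** **Gamification I teams.** A reader might infer from "group competitions where the total number of steps is compared among the different groups of app users" that trial participants are formed into teams whose steps are pooled, so that the whole gamified arm is clustered. The text does not support this. It refers to groups of users of a public app, and a participant's group may contain no other participant. This objection stands, and the concern for B and D is conditional.

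**Sign.** Standard errors need not be too small. Rivalry and rankings could produce a negative correlation, and the protocol gives no ICC. This stands, so the claim is conditional on a positive ICC. With either sign, independence is the wrong assumption.

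**Size.** The pooled contrasts, listed first in the Data analysis section, barely move if only meetings cluster. Recruitment from 15 October 2018 to 15 November 2020 is about 109 weeks. If entry were even, only about 7 × 6/109 = 0.4 people would be in the six-week group-3 phase at once, so a concurrent group of 7 would be unlikely in the pilot. Uneven entry would raise this. The group of 7 is therefore near the upper end for the pilot, and larger groups do not fit an expected group-3 total of about 7.

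**Left to the analysis plan.** Degrees of freedom and correlation structure often are, and the article is condensed. Part of this stands. But the article names its method and contrasts, and the method as stated does not suit those containing C or F.

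**Sizing.** It is tempting to say that the later trial will be underpowered. The documents do not support that: they state no power, the later size is not yet calculated, and the inputs listed do not exclude a design effect.

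**Conclusion.** The point holds in a limited form. Group 3 is partly group-delivered, control is not described as such, and the stated ANOVA ignores the difference. Given a positive ICC, the standard errors for contrasts containing C or F are too small. The inflation of a nominal 5% error ranges from negligible at ICC 0.01 to moderate at 0.10. It is clearest for C and F taken alone and slight for the pooled arms. These figures rest on assumed ICCs, a single meeting group, equal re-randomisation and a normal approximation. The change is worth making because it is cheap and membership may not be recoverable later, not because any figure in the protocol is wrong.

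**What to change.** 1. Record each group-3 participant's meeting group, with dates of membership, and state how the groups are formed. Record the competition team too if trial participants share one.
2. For contrasts that include group 3, replace plain ANOVA with a partially nested mixed model: a random group effect for group-treated participants only, with small-sample degrees of freedom. Extend it to B and D only if shared teams are recorded.
3. In the pilot there will be too few groups to estimate an ICC, and with a single group its effect cannot be separated from the treatment's. There, report the affected contrasts also at fixed ICCs of 0.01, 0.05 and 0.10.
4. Carry the same ICC range, with the intended group size, as a stated assumption when the later trial is sized.

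The cost is one data field (two if teams are shared), a modest change of analysis and slightly wider intervals for the affected contrasts. The pilot size and the interventions do not change.
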